## Abstract

**Background:**

Though rates of tobacco smoking have decreased consistently over the past 3 decades, cigarette use remains the top preventable cause of premature death in North America. The Clinical Effort Against Secondhand Smoke Exposure (CEASE) is a medical clinic-based intervention that systematically screens parents for tobacco use and offers them direct access to evidence-based smoking cessation services. While the effectiveness of CEASE for parents who smoke has already been demonstrated in the United States, the CEASE model has not yet been tested in Canada, among parents who use e-cigarettes, or among adolescents who use cigarettes and e-cigarettes.

**Objective:**

We aim to demonstrate the feasibility and evaluate the preliminary effectiveness of the CEASE program for parental smoking cessation and its adapted version for adolescent smoking cessation and adolescent and parental vaping cessation.

**Methods:**

We will approach parents or guardians of children aged between 0 and 17 years, as well as adolescent patients aged between 14 and 17 years, from a tertiary care pediatric hospital in Montreal, Quebec, Canada, for participation in this single-blinded, pilot randomized controlled trial. Eligible participants are those who report using tobacco cigarettes or e-cigarettes at least once in the last 7 days and present to an outpatient pediatric clinic for a scheduled appointment. Our recruitment target is 100 participants: 50 parents or guardians of children aged 17 years or younger, and 50 adolescents aged between 14 and 17 years. The feasibility of implementation of the CEASE model will be measured by recruitment and retention rates for all 4 participant groups (stratified as follows: parents who use cigarettes, parents who use e-cigarettes exclusively, adolescents who use cigarettes, and adolescents who use e-cigarettes exclusively). Parent and adolescent participants within each group are randomized to the intervention and control groups using a 1:1 ratio through a computer-generated randomization list. Preliminary effectiveness outcomes include self-reported smoking and e-cigarette cessation, use of cessation resources, changes in smoking and e-cigarette use, motivation to quit, and quit attempts among participants. Participants complete electronic questionnaires on a tablet in the clinic at baseline as well as electronic follow-up questionnaires at 1, 3, and 6 months. Individuals reporting successful quit attempts are invited to provide a urine sample for cotinine testing to biochemically confirm quit. Analyses include descriptive statistics as well as exploratory trajectory analyses of smoking, e-cigarette use, and motivation to quit.

**Results:**

Research activities began in June 2022. Participant enrollment and data collection began in February 2023 and are expected to be completed in 15 months.

**Conclusions:**

There is a strong need for effective and cost-effective smoking and vaping cessation interventions for parents and adolescents. If successful, this study will help inform the preparation of a fully powered randomized controlled trial of CEASE in Canada in these populations.

**Trial Registration:**

Clinicaltrials.gov NCT05366790; https://www.clinicaltrials.gov/study/NCT05366790

**International Registered Report Identifier (IRRID):**

DERR1-10.2196/47978

## Introduction

Tobacco use is the single greatest preventable cause of morbidity and mortality in Canada, accounting for 48,000 deaths and CAD $16.2 billion (US $11.9 billion) in attributable health-related costs annually [1,2]. Smoking is a significant risk factor for multiple cancers [3] as well as cardiovascular diseases [4], thus shortening the life expectancy of smokers who initiate during adolescence by more than 10 years [4]. Despite parental smoking being an important risk factor for child initiation of tobacco (children of parents who smoke have 4-fold greater odds of becoming smokers when compared with children of nonsmoking parents) as well as for the development of several illnesses, such as bronchiolitis, asthma exacerbations, and pneumonia [5], about 15% of Canadian children are still exposed to household secondhand smoke [6]. Parents are thus an important target for smoking cessation interventions to improve their own health and protect that of their children and future generations. Given that 90% of smokers start smoking before the age of 18 years [7], adolescence represents a critical period to intervene in the fight against smoking [8].

Smoking among adolescents and young adults remains common despite rates decreasing over the past 3 decades, and adolescent use of nicotine-containing e-cigarettes (hereafter referred to as e-cigarettes) has shown a worrying increase over the past 10 years [9]. Most adults who use e-cigarettes (e-cigarette use is referred to interchangeably with vaping) do not have a history of tobacco use; however, once vaping has been initiated, the risk of subsequent tobacco, alcohol, and drug use increases [9]. Commonly used e-cigarettes usually contain high concentrations of nicotine, and while potentially effective for adult smoking cessation [10], they are not effective for youth smoking cessation and should not be recommended in this population [11].

In 2019, more than half of smokers in Canada (57.9%) reported seriously considering quitting in the next 6 months, and 26.9% were considering doing so in the next month [12]. Similarly, the majority of adults and adolescents who use e-cigarettes report that they intend to quit vaping [13,14]. Individuals trying to quit without behavioral support or smoking cessation medication (eg, nicotine replacement therapy [NRT]) can face great challenges due to nicotine’s addictive nature and severe psychological and physical withdrawal symptoms [3]. Several evidence-based smoking cessation interventions exist, including behavioral and pharmacological treatments that can be used alone or in combination [15], which greatly increase the odds of successfully quitting [16], and even more so when behavioral and pharmacological (NRT) interventions are combined [17]. Behavioral support traditionally refers to counseling; however, newer modalities, such as SMS text messages and app-based interventions, have shown promise [16] and would provide individuals with personalized, accessible behavioral support in quitting at low to no cost.

Health care providers can enhance the success of quit attempts by offering assistance and facilitating access to smoking cessation interventions [18]. Through their regular contact with families, pediatric health care providers are in a unique position to assist parents and adolescents in quitting smoking and vaping. However, studies and clinical experience show that pediatric health care providers rarely capitalize on this opportunity [19]. Lack of time, lower perceived priority of smoking or e-cigarette cessation relative to other care, fear of upsetting families, and lack of perceived efficacy are among the reasons why this type of intervention is rarely provided [20]. Digital preappointment screening questionnaires to identify individuals who smoke or vape and connect them with existing resources are a promising avenue to deliver cessation interventions in pediatric clinics [21]. This approach is well-accepted by patients and health care providers [21].

The Clinical Effort Against Secondhand Smoke Exposure (CEASE) intervention is an effective and cost-effective medical clinic-based intervention that systematically screens parents for tobacco use and offers them direct access to evidence-based smoking cessation services [22,23]. The model has been studied in the United States with promising results. A cluster randomized trial showed a 3.7% decrease in smoking prevalence between the intervention and control groups over a 2-year observation period (2.7% decrease in smoking rates in the intervention group vs 1.1% increase in the control group; difference –3.7%, 95% CI –6.3% to –1.2%; [23]). Cost-effectiveness data from Drouin et al [22] also showed that the incremental cost per quit (among adult participants who smoked) was US $1132 compared with usual care, a much lower figure than other clinical care-based smoking cessation interventions.

The primary objectives of this pilot randomized controlled trial of CEASE are to demonstrate the feasibility and preliminary effectiveness of CEASE for adults who smoke tobacco and its adapted version for parents with e-cigarette use and adolescents with cigarette and e-cigarette use in Canada. This pilot trial seeks to accomplish the following three aims: (1) evaluate the feasibility and effectiveness of the CEASE model in the Canadian setting, which differs from the United States in pediatricians’ scope of practice, financial incentives for physicians, and insurance coverage for NRT [24]; (2) address the gaps in knowledge regarding vaping cessation, for which many professional societies recommend using similar cessation tactics, strategies, and resources as with regular tobacco cigarettes [11,25]; and (3) validate the feasibility of recruiting participants in proposed sites of care (hospital-based pediatric clinics) and obtaining data on quit interest and intent in this population.

This pilot randomized controlled trial of CEASE in Canada aims to answer these questions by recruiting parent and adolescent participants from hospital-based pediatric clinics and randomizing them to the CEASE program or usual care.

## Methods

### Study Design, Setting, and Participants

This is a single-center, pragmatic, single-blind, pilot randomized controlled trial comparing the CEASE intervention to usual care (control condition). Participants will be recruited over a 9-month period and followed for 6 months (15-month study period). Figure 1 shows the study flow diagram. This study is being conducted in various clinics within the Sainte-Justine University Hospital Centre, (Montreal, Quebec, Canada), including the general pediatrics clinic, the adolescent medicine clinic, and the orthopedics and sports medicine clinics.

**Figure 1 figure1:**
[figure not shown]
Study flow diagram illustrating participant trajectory through study of a brief digital screening and intervention tool for parental and adolescent tobacco and electronic cigarette use. CEASE: Clinical Effort Against Secondhand Smoke Exposure.

The recruitment target is 100 individuals who report using tobacco or e-cigarettes (either tobacco or e-cigarettes alone, or both tobacco and e-cigarettes) in the 7 days before responding to the study questionnaire. A minimum of 50 parents and 50 adolescents will be recruited.

The study will be reported according to the Strengthening the Reporting of Observational Studies in Epidemiology Statement: Guidelines for Reporting Observational Studies [26].

### Recruitment

The appointment schedules of participating clinics will be reviewed the week before by the research team, and a recruitment schedule will be made according to the clinical volume of each clinic to maximize the number of potential patients approached. At the time of registration for their scheduled appointment, parents or legal guardians (hereafter referred to as parents) of children aged between 0 and 17 years as well as adolescents aged between 14 and 17 years are approached by a research assistant in the clinic waiting room to complete the screening survey on an electronic tablet. The survey is preceded by an abbreviated consent form. This approach is similar to that which was successfully used in CEASE studies in pediatric primary care in the United States [23]. Parents and adolescents are asked sociodemographic, smoking, and e-cigarette screening questions (see “Inclusion and Exclusion Criteria” section). Participants who respond “yes” to at least 1 of the 2 screening questions are invited to participate in the CEASE pilot study and have access to the full consent form. These forms are available in the Multimedia Appendix 1. During the entire study period, research assistants keep a detailed recruitment log, including information on participant screening, eligibility, recruitment, randomization, and retention in the study.

### Inclusion and Exclusion Criteria

#### Inclusion Criteria

Parents of children aged between 0 and 17 years who smoke cigarettes or use nicotine-containing e-cigarettes. Users are defined as those who answer “yes” to at least 1 of the 2 screening questions: (1) Have you smoked a single cigarette, even a puff, in the past 7 days? (smoking), and (2) Have you used an e-cigarette or vaping device containing nicotine, even a puff, in the past 7 days? (vaping).

Parents are eligible if (1) they are aged 18 years or older, (2) their child is aged between 0 and 17 years, (3) they are attending a regular scheduled medical appointment, and (4) they are sufficiently proficient in either French or English to be able to read and answer a written questionnaire. Informed consent is obtained before data collection.

Adolescent users are defined as those who answer “yes” to at least 1 of the above screening questions.

Adolescents are eligible if they are aged between 14 and 17 years, meet the aforementioned 3rd and 4th criteria, and have provided informed consent (in Québec, adolescents aged 14 years can provide consent).

#### Exclusion Criteria

Adolescents whose parents (if present) are not agreeable to their participation and families presenting to the clinic for an urgent medical issue will be excluded.

In each age category, a total of 2 participant groups are formed: “smokers,” defined as all users reporting past 7-day use of traditional combustible cigarettes, with or without e-cigarette use, and “e-cigarette-only users,” who report exclusive use of e-cigarettes. E-cigarettes include any electronic nicotine delivery systems, for example, vape pens, e-pens, e-cigars, e-pipes, or vaporizers containing nicotine. This division was created on the basis that the CEASE model has only been tested in individuals who report cigarette use (with or without e-cigarette use) but has not yet been tested in individuals using exclusively e-cigarettes [22].

### Intervention

#### The CEASE Intervention

The CEASE intervention is an evidence-based parental smoking cessation intervention delivered in pediatric practices, leveraging existing health care and community resources [23]. In this project, CEASE is delivered through electronic tablets in pediatric clinic waiting rooms. It integrates evidence-informed tobacco (cigarette) and vaping (e-cigarette) product use screening and cessation assistance into routine visits to pediatric clinics. This workflow, used by [name] et al [19] in the United States, requires less than 10 minutes to complete, does not disrupt clinic flow, can be sustained over a 2-year period, and is acceptable to families and health care providers. CEASE is based on the 5As (ask about smoking, advise to quit, assess readiness to quit, assist with a quit plan, and arrange follow-up) model of smoking cessation. Given that CEASE is a 1-time intervention, “arrange” is removed, and the fourth step “assist” is divided into 2 parts: (1) providing behavioral support (in-person, phone, SMS text message, or app quit support) and (2) providing pharmacological support (access to NRT). Specifically, CEASE includes the following steps:

Ask (routine, systematic identification of smokers and e-cigarette users)Advise (brief motivational intervention)Assess (self-assessment of readiness and quitting preferences)Assist (support to quit for those interested)Behavioral supportPharmacological support (NRT)

#### Ask: Routine, Systematic Identification of Smokers and E-Cigarette Users

Families with a scheduled appointment are approached by a research assistant and prescreened for eligibility using a brief anonymous survey on the secure REDCap (Research Electronic Data Capture; Vanderbilt University) platform. Eligible participants are randomized to either (1) the intervention (CEASE) or (2) the control (usual care condition).

#### Advise: Brief Motivational Intervention

Brief motivational interventions have been shown to improve quit rates and may include goal setting, setting a quit date, secondhand smoke education (shown to increase acceptance of services), and enlisting social support. After collecting data on participant smoking and vaping behaviors (a baseline questionnaire delivered through an electronic tablet), CEASE will automatically include brief motivational messages describing the main short- and long-term health benefits of smoking cessation to increase participant engagement and acceptance of services [23].

#### Assess: Self-Assessment of Readiness and Quitting Preferences

Next, participants are invited to indicate whether they are interested in trying behavioral (eg, in-person, phone, SMS text message, or app-based) or pharmacological (ie, NRT) interventions to help them quit or cut down.

#### Assist: Support to Quit for Those Interested—Behavioral Support

In-person or phone quit line support is offered through the government-funded and evidence-based smoking cessation internet platform “J’Arrête (I Quit Now),” provided by the Conseil Québécois sur le Tabac et la Santé (CQTS). Interested individuals can sign up for cessation services directly on the website [27]; study participants have the opportunity to do so directly on the electronic tablet. The Canadian Cancer Society’s (CCS) Short Messages Against Tobacco [28], available from the J’Arrête (I Quit Now) website, is also presented as an option for participants who are interested in receiving SMS text messaging support to help them quit. Participants are offered to sign up to the “J’Arrête (I Quit Now)” web-based app, which provides a platform for the creation and realization of their smoking quit plan, as well as a dashboard to track their progress, trophies, tricks, and a variety of exercises to help overcome smoking cravings. In the week following the completion of the baseline questionnaire, interested participants receive an email or SMS text message reminder with information on how to access the behavioral resources they selected. All in-person, web-based, and SMS text messaging services are available in French and English for both adults and adolescents who smoke and use e-cigarettes. After signifying their interest in signing up for either of these services, participants are asked to consent to their information being transferred to the CCS or to the CQTS, which may contact them in the future and offer them additional smoking or vaping cessation resources.

#### Assist: Support to Quit for Those Interested—Pharmacological Support

CEASE automatically generates a written recommendation for NRT [23], to be discussed with a community pharmacist, including for those cutting down to quit as recommended in the latest national and international guidelines [29]. Since the best practice for NRT is to provide both a long- (ie, patch) and short-acting form (eg, gums or lozenges), a recommendation for 2 forms of NRT is automatically populated and printed in the clinic, provided to the participant, and sent to the participant by email. Given that pharmacists can now prescribe NRT in Quebec, the recommendation is written as detailed instructions for the pharmacist to prescribe NRT for a period of 3 months (the time period covered by public medical insurance in Quebec) and adjust the dosage based on the participant’s reported use of tobacco or e-cigarettes. Study investigators remain available to support community pharmacists as needed.

The role of the provider in this intervention is adjunctive and not necessary to trigger intervention delivery. As such, CEASE is a standalone intervention and can take place without any provider involvement.

#### Control Condition

The control condition is care as is usually delivered in participating clinics. Current practice at those sites does not currently include routine provision of assistance for parental nor adolescent smoking and e-cigarette cessation (eg, referral to quit lines and NRT prescription). Participants in the control conditions will complete the same questionnaire as those in the intervention group; however, they will not be presented with a list of resources at the end of the questionnaire. While completing the final 6-month follow-up questionnaire, participants in the control group will be offered the option to receive a 1-time direct linkage to CEASE smoking and vaping cessation resources (behavioral supports and NRT recommendation).

### Data Collection and Compensation

After consenting to the study, participants are asked to fill out a baseline questionnaire on an electronic tablet. Participants randomized to the intervention group have the option of receiving direct access to the CEASE evidence-informed cessation resources (if interested) after completing their questionnaire, while those randomized to the control group are only offered access to these resources at the end of the 6-month follow-up period (see “Control Condition” section). Participants in both groups are followed for 6 months following recruitment, with data collection at 1, 3, and 6 months (and the possibility of obtaining direct access to evidence-informed resources at each time point, if interested, for participants in the intervention group). Data collection tools (questionnaires) are available upon reasonable request to the corresponding author. Participant confidentiality is protected by limiting the collection of identifying information to an email address and phone number; date of birth, name, or participant address will not be collected. All data are stored on the secure web-based REDCap platform and in study logs on the Sainte-Justine University Hospital Centre server without participant-identifying information. Only the study investigators will have access to this data set at the end of the study period.

At each time point, participants are contacted by the study team by email, phone, or SMS text message (based on their preference) with a notification to complete the follow-up survey through REDCap, a secure web-based platform. If participants declare an abstinence of 7 days or more and consent to undergoing urine cotinine testing, they are contacted to arrange for biochemical confirmation of smoking cessation (cotinine testing) [30]. Data for confirmatory smoking or vaping cessation testing (urinary cotinine testing results) is sent directly to the study coordinator (to maintain investigator blinding) using a secure web-based portal. Participants will be called by research assistants and sent reminder emails or SMS text messages (based on their preference) to bolster the completion of follow-up questionnaires. They will receive CAD $10 (US $7.31) in compensation for each survey completed and an additional CAD $20 (US $14.62) per urine sample provided for cotinine testing.

Recruitment is expected to last a period of 9 months, with an additional 6 months required for follow-up with all recruited participants to complete data collection. The data analysis will begin with the end of recruitment and is expected to be completed in the 9 months following the final participant follow-up, for a total of a 24-month study period.

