**Protocol fidelity**								
	Baseline questionnaire completion	Proportion of participants who complete the baseline questionnaire out of randomized participants (REDCap^a^ survey)	✓				Baseline questionnaire	≥90%
	Access to web-based resources	Proportion of participants who want to be connected to the web-based resources who report access these resources (self-report)	✓	✓	✓	✓	Baseline and follow-up questionnaires	N/A^b^
	Access to quit lines (phone, or SMS text messaging support)	Proportion of interested participants who received a communication from the quit lines (self-report)		✓	✓	✓	Baseline and follow-up questionnaires	N/A
	Access to NRT^c^	Proportion of participants who want to receive NRT who receive a report receiving a formal written recommendation or prescription for NRT	✓	✓	✓	✓	Baseline and follow-up questionnaires	N/A
	NRT use	Proportion of participants who have used NRT (self-report)		✓	✓	✓	Baseline and follow-up questionnaires	N/A

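### Urine cotinine cannot confirm quitting in participants using the NRT that only the intervention arm is recommended, so a cotinine-confirmed comparison would be biased towards no effect

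*Protocol article*

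**What the plan says.** Under Data Collection and Compensation, the trigger is a self-declared quit of at least a week, plus agreement to give urine. What follows for these participants is: "they are contacted to arrange for biochemical confirmation of smoking cessation (cotinine testing". The abstract gives the purpose: "Individuals reporting successful quit attempts are invited to provide a urine sample for cotinine testing to biochemically confirm quit". Table 2 (Study retention) schedules cotinine results at 1, 3 and 6 months. No condition is set on NRT or vaping at the time of sampling.

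The pharmacological step of the intervention is described thus: "CEASE automatically generates a written recommendation for NRT". It covers a long-acting and a short-acting form and is written as "detailed instructions for the pharmacist to prescribe NRT for a period of 3 months". Under Data Collection and Compensation, intervention participants can reach the resources again at each follow-up. Under Control Condition, usual care does not routinely include NRT, and controls are offered the link to resources while completing the 6-month questionnaire.

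The smoker stratum is defined by "past 7-day use of traditional combustible cigarettes, with or without e-cigarette use", so it contains dual users. Table 2 also records, at each follow-up, smoking and vaping status and "Proportion of participants who have used NRT (self-report".

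**The concern.** The marker and the intervention work against each other. A participant who follows the trial's pharmacological advice and stops smoking or vaping still takes in nicotine during the course, and cotinine shows it. The article's means of confirming a quit therefore fails in people for whom the intervention may have worked. Because allocation decides who is given the NRT recommendation, the failure falls mainly in one arm.

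At stake is the reading of the pilot's effectiveness signal. The Analyses section plans exploratory between-arm comparisons to look for trends, and the Conclusions say the data will inform a fully powered trial. A confirmed quit rate depressed mainly in the intervention arm would make the programme look weaker than it is.

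There is a second, separate problem. In the smoker stratum, a dual user who stops cigarettes but still vapes cannot be confirmed as a non-smoker by cotinine. This happens in both arms.

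**Working it through.** **No plan figure to reproduce.** The article gives no quit rate, NRT uptake or cotinine cut-off. The check compares the timings and then illustrates the size with assumed inputs.

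**Timing of NRT against the tests, intervention arm**

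- Course started at baseline: months 0 to 3. It covers the 1-month test and reaches the 3-month test, and is over by the 6-month test.
- Course started at the 1-month contact: months 1 to 4. It covers the 3-month test.
- Course started at the 3-month contact: months 3 to 6. It reaches the 6-month test.

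In the control arm the trial prompts no NRT before the 6-month questionnaire. The arms therefore differ most at 1 and 3 months, and at 6 months only through later starts.

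**Illustration of size**

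Assumptions: any current nicotine source gives a positive result; every quitter consents to testing; a positive result counts as not confirmed. There are about 50 participants per arm (target of 100, allocated 1:1).

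Confirmed rate = true quit rate × (1 − share of quitters on NRT at the test).

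True rates 20% (intervention) and 10% (control), no NRT among control quitters:

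| Intervention quitters on NRT | Confirmed, intervention | Confirmed, control | Difference (true: 10 points) | Intervention quitters missed, of 50 participants |
|---|---|---|---|---|
| 10% | 0.20 × 0.9 = 18% | 10% | 8 | 1 |
| 30% | 0.20 × 0.7 = 14% | 10% | 4 | 3 |
| 50% | 0.20 × 0.5 = 10% | 10% | 0 | 5 |

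If 10% of control quitters also use NRT, the control rate is 0.10 × 0.9 = 9%, and the differences become 9, 5 and 1 points.

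If the true rates are equal at 15%, 30% of intervention quitters are on NRT and no control quitters are, the confirmed rates are 0.15 × 0.7 = 10.5% and 15%. That is a spurious −4.5 points.

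**Dual use, both arms**

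Suppose 20% of quitters in each arm still vape. Both confirmed rates are multiplied by 0.8, so 20% and 10% become 16% and 8%. The ratio stays at 2 and the difference shrinks from 10 to 8 points. Continued vaping at the same rate in both arms lowers the confirmed rates in proportion; it creates no imbalance between arms.

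**The case against.** The strongest reply is that the article does not define a cotinine-verified endpoint. The abstract names cessation as self-reported, Table 2 lists only the availability of cotinine results with no threshold, and the Analyses section does not mention cotinine. Nothing says that a positive result overrides self-report. This stands. A reader might infer that true quitters are misclassified in the trial's cessation outcome, but the documents support only a conditional statement: the bias arises if cotinine is used for the confirmation that the article describes.

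A reader might also infer that the trial supplies nicotine to one arm. It does not. It issues a recommendation for a community pharmacist to act on, for interested participants, and uptake is unknown. Nor is NRT confined to one arm with certainty: under Strengths and Limitations, the article accepts that controls may seek out public resources themselves. That narrows the contrast, as the 9, 5 and 1 point results show.

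Dual use might be read as adding to the imbalance between arms. It does not support that reading, because randomization is 1:1 within the smoker stratum (Allocation) and dual users are expected in both arms. The article also describes the assay as testing smoking or vaping cessation; for a dual user who still vapes, a positive result is misleading only when the claim is about cigarettes.

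Finally, reading rules for an ancillary assay can be left to an analysis plan. That would answer a complaint about missing detail. Here, however, the article fixes the marker, trigger, timing and purpose, and the marker cannot serve that purpose in NRT users. A later document could limit the harm, but the confirmation as stated would remain invalid for them.

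**Conclusion.** The point holds in a limited form. Cotinine cannot confirm abstinence in a quitter using NRT, and the trial promotes NRT in the intervention arm alone until the 6-month questionnaire. Any cotinine-confirmed comparison would be biased against the intervention, hence towards no effect where the intervention works, mainly at 1 and 3 months.

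The size is not known from the documents. The loss of 2 to 10 points from a true 10-point difference rests on assumed quit rates, assumed NRT use of 10% to 50% among intervention quitters, none among control quitters, and complete testing.

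The reach is modest. The primary outcome (recruitment rate) and the progression threshold of 6 parents and 6 adolescents per month do not depend on cotinine. The cessation comparison is exploratory, self-reported and acknowledged to be underpowered. It is still worth correcting, because a confirmed rate reported without this qualification could mislead the planning of the full trial.

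**What to change.** State the following in the analysis wording:

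1. Product-specific self-reported 7-day abstinence, separately for cigarettes and e-cigarettes, is the between-arm cessation comparison at each visit.
2. Cotinine confirms or refutes self-report only in participants reporting no NRT and no nicotine vaping at sampling.
3. A positive result with reported NRT use, or with reported vaping when cigarette abstinence is the claim, is classed as not verifiable rather than as a failed quit.
4. Cotinine-confirmed results are a sensitivity analysis, with the number not verifiable shown by arm and visit.

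The NRT-use and smoking and vaping status items in Table 2 are already collected at 1, 3 and 6 months, so no new assay is needed. The questionnaires are not shown. If the NRT item does not identify use at the time of sampling, a question asked with the urine sample would be needed. The downside is that fewer participants will have a verified status, chiefly in the intervention arm at 1 and 3 months.
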